### Measures

The outcome measures will take participants approximately 20 min to complete (Table 1).

**Table 1 Tab1:** Baseline (BL) and follow-up measures assessment schedule

Instrument	Domain	BL	6 weeks	15 weeks
DASS 21	Psychological wellbeing	x	x	x
Satisfaction with Life Scale (SWLS)	Quality of life	x	x	x
The Flourishing Scale (FS)	Psychological wellbeing	x	x	x
Brief-COPE	Stress and distress management	x	x	x
Use of online delivery methods (session summary sheet)	Delivery experience		x	
Number and length of sessions attended Sessions delivered (Session summary sheet)	Feasibility Fidelity		x	
Experience interviews	Acceptability			x

### Demographics

Age, gender, ethnicity, living arrangements, financial support, years of education, relationship status and relationship to the relative, mental health diagnosis of relative will be collected.

### Depression, Anxiety, and Stress Scale (DASS-21)

The DASS-21 [20] is a 21-item self-report questionnaire designed to measure the domains of depression, anxiety and stress. Each subscale contains 7 items rated on a four-point Likert scale. Higher scores indicate more severe symptoms. The DASS-21 is reported to have high internal consistency for each of the subscales (depression, *r* = 0.88; anxiety, *r* = 0.82; stress *r* = 0.90), and the total scale (*r* = 0.93) [21].

### Satisfaction with Life Scale (SWLS)

This is a widely used 5-item self-report measure of life satisfaction [22]. The scale includes a cognitive judgment component and an emotional component. The SWLS uses a 7-point Likert scale from 1 (strongly disagree) to 7 (strongly agree). The range of possible scores is from minimal satisfaction with life (5) to very high satisfaction with life [22]. The SWLS has demonstrated convergent validity with other self-report measures of life satisfaction, including the Philadelphia Geriatric Center Morale Scale [23]. The SWLS appears to identify a single life satisfaction factor. Internal consistency is good with a Cronbach’s alpha coefficient of 0.83 [23].

### The Flourishing Scale (FS)

The FS is an eight item self-report measure of psychological well-being [24]. The scale concepts include feelings of competence, positive relationships, and purpose in life. Respondents rate on a 7-point Likert scale from strong disagreement to strong agreement with statements. Scores range from 8 to 56 and high scores indicate positive self report of wellbeing [25]. The scale developers report strong correlations with other psychological well-being scales and good internal consistency with Cronbach’s alpha coefficient of 0.87 [24].

### Brief-COPE

The Brief-COPE is a 28 item self-report questionnaire designed to measure effective and ineffective ways to cope with a stressful life event [26]. “Coping” is defined broadly as an individual’s effort used to minimise distress associated with problems in life. The scale identifies a person’s primary coping styles via scores on fourteen factors across three subscales: Problem-Focussed Coping; Emotion-Focussed Coping and Avoidant Coping [26]. Effective coping strategies are linked to good self-esteem, lower perceived stress, and lower psychological distress, whereas less functional strategies (for example denial, substance use and/or self-blame) are linked to poor self-esteem, to higher perceived stress, and to psychological distress [27]. The 14-factor structure of the Brief COPE has good psychometric properties [28].

#### Treatment fidelity and feasibility

All counsellors delivering CRAFT for The Family Empowerment Program will be required to be certified as CRAFT Therapists following standardised procedures established by Robert Meyers [18]. Each counsellor will complete a session summary sheet for each client (see Supplementary Material) for each session. The summary sheet will record which CRAFT procedures were delivered and also identify any problems experienced with the online delivery.

#### Treatment acceptability

Treatment satisfaction will be evaluated via individual interview with participants at the 15-week follow-up. All participants who have completed at least one session of the program will be invited to an interview about their experiences with the program and any related benefits and challenges. Acceptability will be further assessed via individual interviews with clincians who have delivered the program. These interviews will be conducted when recruitment has finished. All clinicians who delivered at least one session will be invited to participate in an interview with the aim of capturing challenges for those who did not regularly deliver the program.

#### Sample size calculation

The study's sample size is determined using data from a previously published cluster randomized trial [29]. Taking into account an outcome of treatment engagement rate of 29% for the online FEP intervention group and 15% for the control group, along with a 5% level of significance (α) and 80% power, the calculated sample size is 216 (with 108 participants in each group). To account for a conservatively estimated attrition rate of 20% during follow-up, a total of 260 participants will be recruited.

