**Methods:**

The trial is a randomized wait-list control trial assessing the effectiveness, feasibility and acceptability of online CRAFT with a parallel group. Participants will be randomised to receive either online CRAFT or to a wait-list control group who are provided with CRAFT related reading material during the waiting period. Outcomes will be assessed at baseline and then at 6- and 15-weeks post baseline. The primary outcome will be improved wellbeing of participating family members. The trial reporting will comply with SPIRIT guidelines.

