## Discussion

This study describes a randomised controlled trial of online delivery of CRAFT, a therapy program for family members concerned about a relative’s substance use. In this program family members whose relative also experiences a mental health condition will be included in the study. There are few substance treatment programs designed for family members even though the family are frequently the ones who provide care and support to people with substance dependence, bearing the brunt of associated health, financial and relationship difficulties [3, 4]. While people with substance problems are not the focus of this study, it does specifically include family members whose relative has both substance dependence and a mental health condition. A similar study [12] found that family members did not know how to talk about substance use with their relative who had a mental illness, even though the substance use was having critically negative effects on their psychiatric treatment. The Family Empowerment Program (CRAFT) offers a structured and tested way to communicate effectively about substance use and its effects, potentially improving mental health treatment for the relative. Any impact in this area will be picked up through the qualitative interviews with participants and will identify areas for future research.

This study will focus on people living in rural areas. Substance treatment programs are limited in rural Australia [8, 9]. The provision of the Family Empowerment Program (CRAFT) online should make family focused substance treatment support accessible and attainable for the first time in many rural areas. The delivery of the program via trained and accredited counsellors assures the fidelity to the CRAFT program and a quality service. These aspects of program delivery will be carefully evaluated through fidelity checklists and follow-up interviews with participants. The outcomes of this trial will have meaningful implications for the future funding and support of family focused substance treatment services that are inclusive of people with mental health conditions.

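### The sample size and its 80% power are for a binary treatment engagement rate, not for the primary outcome of family-member wellbeing, which has no power statement

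*Protocol article*

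**What the plan says.** The Sample size calculation takes its assumptions from an earlier study: "The study's sample size is determined using data from a previously published cluster randomized trial". The outcome and rates are: "Taking into account an outcome of treatment engagement rate of 29% for the online FEP intervention group and 15% for the control group". The error rates follow, "along with a 5% level of significance (α) and 80% power", without saying whether the test is one- or two-sided. The result is 216, or 108 per group. Attrition is then added: "To account for a conservatively estimated attrition rate of 20% during follow-up, a total of 260 participants will be recruited".

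The rest of the article is about another outcome.

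- **Abstract, Methods:** "The primary outcome will be improved wellbeing of participating family members".
- **Objectives of the study:** the hypothesis and Aim 1 concern self-reported depression, anxiety, stress and life satisfaction. Treatment engagement is in none of the hypotheses or aims.
- **Measures, Table 1** ("Baseline (BL) and follow-up measures assessment schedule"): the DASS-21, Satisfaction with Life Scale, Flourishing Scale and Brief-COPE are scheduled at baseline, 6 and 15 weeks. The only related entries are the number and length of sessions attended and the sessions delivered, listed at 6 weeks under feasibility and fidelity.
- **Statistical analysis:** effects on primary outcomes come from mixed-effects regression, with mean differences for continuous variables and relative risks for categorical ones.
- **Discussion:** the people with the substance problem are described as not being the study's focus. On possible benefit to the relative's mental health treatment, it says: "Any impact in this area will be picked up through the qualitative interviews with participants".

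**The concern.** A power statement is useful only for the outcome it was computed on. Here the one outcome with a power calculation is absent from the aims and from the assessment schedule, and the outcome that the trial sets out to test has none. The 80% figure is the article's only justification for recruiting 260 people, and a reader would naturally attach it to wellbeing.

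What is at stake is interpretation. If the wellbeing result is null, nothing in the plan says what difference the trial was able to detect. A 14-point difference in a proportion does not translate into a difference on the DASS-21 or the Satisfaction with Life Scale.

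**Working it through.** **1. Reproduce the plan's figure.** Inputs from the Sample size calculation: p1 = 0.29, p2 = 0.15, alpha 5%, power 80%. The mean proportion is 0.22. The usual formula per arm, without continuity correction, is

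n = [z_alpha × √(2 × 0.22 × 0.78) + z_power × √(0.29 × 0.71 + 0.15 × 0.85)]² / 0.14²

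The two roots are 0.5858 and 0.5774, and z_power = 0.8416.

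- One-sided 5% (z = 1.645): n = 107.2, rounded up to 108 per arm, 216 in all. This matches the plan.
- Two-sided 5% (z = 1.960): n = 136.3, rounded up to 137 per arm, 274 in all. This does not match. With 108 per arm, two-sided power is about 70%.

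For the two-sided test, the unpooled, arcsine and continuity-corrected variants give 134, 135 and 151 per arm, so none of them yields 108 either.

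**2. Attrition.** 216 × 1.2 = 259.2, rounded up to 260. Losing 20% of 260 leaves 260 × 0.8 = 208, or 104 per arm. That is 8 below the 216 in the plan; 216 / 0.8 would be 270.

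**3. What 260 means for a continuous wellbeing score.** The article gives no target difference and no SD for any scale, so differences are in SD units. Assumptions: 104 per arm, two-sided 5%, one scale at one time point, no baseline adjustment unless stated. The detectable difference at 80% power is approximately

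d = (1.960 + 0.842) × √(2/104) = 0.389

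The exact calculation with the noncentral t distribution gives 0.390.

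| Setting, 104 per arm | Detectable difference at 80% power |
|---|---|
| Unadjusted, 5% | 0.39 SD |
| Baseline-adjusted, r = 0.5 (assumed): 0.390 × √(1 − 0.25) | 0.34 SD |
| Baseline-adjusted, r = 0.7 (assumed): 0.390 × √(1 − 0.49) | 0.28 SD |
| Unadjusted, four scales at 1.25% each | 0.47 SD |

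**4. Power at assumed true differences.** Power ≈ Φ(d × √(104/2) − 1.960), with √52 = 7.211, unadjusted:

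| True difference | d × 7.211 − 1.960 | Power |
|---|---|---|
| 0.2 SD | −0.518 | 30% |
| 0.3 SD | 0.203 | 58% |
| 0.4 SD | 0.924 | 82% |
| 0.5 SD | 1.646 | 95% |

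**5. Number needed on the same assumptions.** For 80% power, after dividing by 0.8 for attrition, the total is 983 at 0.2 SD, 438 at 0.3, 248 at 0.4 and 158 at 0.5. The right number for the primary outcome cannot be fixed from the document, because it depends on a target difference that is not stated.

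**The case against.** The strongest reply is that this is a condensed article, and that a full protocol or SAP may hold a wellbeing calculation. That would excuse silence. Here the article gives a complete calculation, with rates, error levels, number and attrition, and attaches it to an outcome other than the one it calls primary. That conflict stands in the text as published.

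A second reply is that 260 may well be enough. This is fair. Power is about 82% at 0.4 SD on a single scale, and baseline adjustment would help. A reader might infer that the trial is underpowered; the document does not support that, because it states no target difference against which to judge.

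Three other stronger readings also go beyond the text.

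- **That the 29% and 15% are certainly the relative's engagement.** The Background and the recruitment section describe the relative entering treatment as a goal of CRAFT, so this is the natural reading, but the Sample size calculation does not say so. If the participant's own engagement were meant, the point would still hold, since that is not the primary outcome. Session attendance is a 6-week feasibility entry, and the control group has a 6-week wait.
- **That engagement cannot be tested at all.** Table 1 lists no such outcome, but the analysis section allows for categorical variables and the supplementary material is not shown. The absence from Table 1 does not prove that nothing is collected.
- **That effects on the relative will be captured solely by interview.** The Discussion sentence does not say solely, and what precedes it concerns mental health treatment, which is not plainly entry into substance treatment.

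**Conclusion.** The point holds. The 80% power and the sample size belong to a binary engagement rate that is not the primary outcome and is not in the assessment schedule, and the article gives no power for family-member wellbeing. For one scale at one time point, with 104 per arm and a two-sided 5% test, the trial has 80% power at about 0.39 SD unadjusted. This is about 0.34 or 0.28 SD with baseline adjustment if the baseline-outcome correlation is 0.5 or 0.7, and about 0.47 SD unadjusted if four scales share the 5% equally. The correlations, the four-way split and the range of true differences are assumptions; the 260 and the 20% are the plan's own.

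The defect is a power claim on the wrong outcome, with adequacy for the right one left unknown. Separately, even for engagement the stated number reproduces only with a one-sided 5% test.

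**What to change.** Replace the engagement-based power claim with one for the primary wellbeing outcome.

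1. **Name the outcome.** The sponsor chooses the scale (total or subscale) and the time point from those already collected. The article does not single out either, so the choice is the sponsor's. Two of its own details bear on the time point: the six sessions may run over 6 to 10 weeks, so some intervention participants may not have finished at week 6, and the control group's wait is 6 weeks, so by week 15 both groups are due to have been offered the program.
2. **State what 260 can detect.** Suggested wording, to be completed: with 260 randomised and 208 evaluable after 20% attrition (104 per arm), the trial has 80% power at two-sided 5% to detect a difference of about 0.39 SD on [scale] at [time point], or about 0.34 SD with baseline adjustment if the baseline-outcome correlation is 0.5. If four scales are to be tested at 1.25% each, give about 0.47 SD unadjusted instead.
3. **Say how that compares with a plausible and worthwhile difference** on the chosen scale, with its SD and source.
4. **If the engagement calculation is kept as secondary,** state that 108 per arm corresponds to a one-sided 5% test, that a two-sided test needs 137 per arm, and that 108 gives about 70% two-sided power.

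The cost is wording: the number recruited and the surveys are unchanged. The drawback is candour. If the plausible effect is below about 0.39 SD, the restated unadjusted power will be under 80%.

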#### Statistical analysis

This study will employ a three-stage analytical approach. In the first stage, baseline characteristics of study participants will be identified using descriptive statistics and standard deviations [30]. The second stage involves bivariable analysis using the chi-square test for categorical variables and the t-test for continuous variables, including the estimation of differences in proportion and mean (difference-in-difference) between intervention groups [30]. To assess the intervention's effects on primary outcomes, mixed effect regression modelling will be applied. Intervention effects will be quantified using mean differences (MD) for continuous variables and relative risks (RR) for categorical variables, along with their corresponding 95% confidence intervals (CI) [31]. The primary results will be based on adjusted effect measures, and all analyses will adhere to the intention-to-treat (ITT) principle [32]. STATA version 18 will be used for the analyses, and statistical significance will be declared by *p*-values < 0.05.

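### The sample size of 216 matches the stated 80% power only under a one-sided 5% test, and 260 does not cover 20% attrition; two-sided power for 29% v 15% is about 69–70%

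*Protocol article*

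**What the plan says.** The Sample size calculation section of the protocol article assumes a "treatment engagement rate of 29% for the online FEP intervention group and 15% for the control group". It sets alpha at 5% and power at 80%, but does not say whether the 5% is one-sided or two-sided. From these inputs it concludes that "the calculated sample size is 216 (with 108 participants in each group". The next sentence sets the recruitment target: "To account for a conservatively estimated attrition rate of 20% during follow-up, a total of 260 participants will be recruited".

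The Statistical analysis section describes "bivariable analysis using the chi-square test for categorical variables and the t-test for continuous variables", effect estimates (mean differences and relative risks) "along with their corresponding 95% confidence intervals (CI", and the rule that "statistical significance will be declared by *p*-values < 0.05". It does not mention a one-sided test.

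**The concern.** The section prints all its inputs, so its result can be checked. Two steps look wrong:

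- **Sample size.** 108 per group is well below what a two-sided 5% test of 29% v 15% needs at 80% power.
- **Attrition.** 260 looks like 216 increased by 20%. That is not the number from which 216 remain after 20% are lost.

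Both errors make the trial smaller than its stated power requires. This is the only justification given for the sample size. If it overstates power, a null result on this comparison would be read as coming from an 80%-power trial when the chance of missing the assumed difference is closer to one in three than one in five.

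**Working it through.** **Inputs** (Sample size calculation section): p1 = 0.29, p2 = 0.15, difference 0.14, mean 0.22, equal groups, alpha 0.05, power 0.80 (z = 0.8416), attrition 20%.

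**Formula** (pooled variance under the null, no continuity correction):

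n per group = [z_alpha × √(2 × 0.22 × 0.78) + 0.8416 × √(0.29 × 0.71 + 0.15 × 0.85)]² / 0.14²

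The square roots are √0.3432 = 0.5858 and √0.3334 = 0.5774.

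**Step 1: reproduce the plan's figure.** With a one-sided 5% test, z_alpha = 1.6449:

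(0.9636 + 0.4860)² / 0.0196 = 107.2, rounded up to 108 per group, 216 in total. This is an exact match.

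**Step 2: the two-sided test.** With z_alpha = 1.9600:

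(1.1482 + 0.4860)² / 0.0196 = 136.3, rounded up to 137 per group, 274 in total. The stated 216 is about 21% below this.

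**Step 3: does another two-sided formula give 216?** No.

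| Two-sided 5%, 80% power | Per group | Total |
|---|---|---|
| Unpooled variance | 134 | 268 |
| Arcsine | 135 | 270 |
| Pooled | 137 | 274 |
| Log odds ratio | 142 | 284 |
| Log relative risk | 147 | 294 |
| Pooled, continuity-corrected | 151 | 302 |

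Rounding of the planning rates does not explain it either. At the most favourable limits of rounding (29.5% v 14.5%) the pooled two-sided formula still needs 119 per group, 238 in total.

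**Step 4: the attrition step.**

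- Number to recruit so that 216 remain after 20% loss: 216 / 0.8 = 270.
- What the plan appears to have done: 216 × 1.2 = 259.2, rounded to 260.
- What 260 leaves after 20% loss: 260 × 0.8 = 208, or 104 per group.
- Loss that 260 can absorb while keeping 216: 1 − 216/260 = 16.9%.

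**Step 5: power for 29% v 15%.** Power = Φ{[0.14 × √n − z_alpha × 0.5858] / 0.5774}. For n = 108 two-sided: (1.4549 − 1.1482) / 0.5774 = 0.531, giving 70.2%.

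| Per group | Situation | Two-sided 5% | One-sided 5% |
|---|---|---|---|
| 108 | the plan's evaluable number | 70.2% | 80.3% |
| 104 | 260 recruited, 20% lost | 68.6% | 78.9% |
| 130 | 260 recruited, none lost | 78.1% | 86.3% |

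Exact binomial enumeration of the two-sided chi-square test gives 71.1% at 108 per group and 69.1% at 104, so the normal approximation is not the cause.

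**The case against.** The arithmetic is not in dispute. The objections concern how far it reaches.

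1. *Two-sidedness is inferred.* The article does not state it, and the hypotheses in the Objectives section are directional. That is true, but directional hypotheses are usual in superiority trials and do not make the test one-sided. A chi-square test of a 2×2 table, 95% intervals and p < 0.05 together describe a two-sided analysis; a one-sided 5% test would correspond to a 90% interval. If one-sided testing was intended, the two sections disagree and still have to be reconciled.

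2. *108 has another possible origin.* A two-sided 5% test at 70% power gives 107.4, which also rounds up to 108. So the source may be a one-sided alpha or a misreported power, and the article cannot tell us which. This stands as a caution about the cause. It does not rescue the text, because 70% contradicts the stated 80%.

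3. *The power figure is for treatment engagement.* The abstract makes family-member wellbeing primary, Table 1 does not list treatment engagement, and the primary outcomes are to be analysed by mixed-effect regression. This stands: 69–70% says nothing about power for wellbeing, for which no effect size or standard deviation is given. That mismatch is a separate defect. It limits what the corrected figure means but leaves the stated figure wrong.

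4. *The attrition slip is small.* This also stands. Against the plan's own 216 it is 8 participants, and it lowers two-sided power only from 70.2% to 68.6%. Most of the shortfall comes from the sidedness.

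**Conclusion.** The concern holds. At the stated 80% power, 216 agrees only with a one-sided 5% test, which the analysis section does not describe. The two-sided requirement is 274 (268 to 302 across the formulas tried). The attrition step is wrong on either reading, because 260 with 20% loss leaves 208, below the plan's own 216.

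For 29% v 15%, two-sided power is about 70% at 108 per group and 69% at 104 (up to about 71% and 70% respectively with other formulas). The type II error risk is therefore about 31%, against the stated 20%. Even with no attrition, 260 gives 78%. On a one-sided reading, the 104 per group left after attrition give about 79%, slightly short of 80%.

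This rests on the article's own planning rates, equal allocation, the two-sided reading of the Statistical analysis section, and treatment engagement as the endpoint compared. It makes no claim about power for the wellbeing outcomes.

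**What to change.** Keep the target of 260 and correct the statement. Suggested wording:

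> With a two-sided 5% significance level, 260 participants will be randomised. Allowing for 20% attrition, 208 (104 per group) will be evaluable, giving about 69% power to detect treatment engagement of 29% v 15%.

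Delete the 80% claim and the step from 216 to 260. If 80% power is to be kept for this comparison, show the correct derivation instead: 274 evaluable, and 274 / 0.8 = 342.5, so 343 randomised (344 for equal arms). If a one-sided 5% test really was intended, say so in both sections, bring the intervals and p-value rule into line with it, and correct the attrition step to 270.

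The correction is best made together with a new calculation based on the wellbeing outcome. If that replaces the engagement calculation, the 69% statement is no longer needed.

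Keeping 260 costs only wording and a less favourable stated power. Restoring 80% two-sided power would take 83 more participants (343 − 260), or 84 for equal arms.
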